## **6. Target parameters**

6.1 Primary endpoints:

Effectiveness of immunoadsorption on symptom burden in patients with post-COVID syndrome measured by the values of:

- Post-COVID-19 functional status scale (PCFS)
- Chalder Fatigue Scale
- Montreal Cognitive Assessment (MOCA)
- MFI-20
- Bell Score
- Strength measurement

and comparison before and after active treatment and before and after sham treatment (before treatment cycle 1/after treatment cycle 1 and before treatment cycle 2/after treatment cycle 2).

6.2 Secondary endpoints:

- Frequency of adverse events under active and sham treatment
- Prevalence of anti-adrenergic and anti-muscarinic autoantibodies in patients with post-COVID syndrome:
  - Proportion of subjects with evidence of anti-α1-adrenoreceptor Abs
  - Proportion of subjects with evidence of anti-α2-adrenergic receptor Abs
  - Proportion of subjects with evidence of anti-β1-adrenoreceptor Abs
  - Proportion of subjects with evidence of anti-β2-adrenergic receptor Abs
  - Proportion of subjects with evidence of anti-β3-adrenoreceptor Abs
  - Proportion of subjects with evidence of anti-M1 acetylcholine receptor Abs
  - Proportion of subjects with evidence of anti-M2 acetylcholine receptor Abs
  - Proportion of subjects with evidence of anti-M3 acetylcholine receptor Abs
  - Proportion of subjects with evidence of anti-M4 acetylcholine receptor Abs
- Concentration of:
  - Anti-α1-adrenoreceptor Abs
  - Anti-α2-adrenoreceptor Abs
  - Anti-β1-adrenoreceptor Abs
  - Anti-β1 adrenoreceptor Abs
  - Anti-β1 adrenoreceptor Abs
  - Anti-M1 acetylcholine receptor Abs
  - Anti-M2 acetylcholine receptor Abs
  - Anti-M3 acetylcholine receptor Abs
  - Anti-M4 acetylcholine receptor Abs

Before and after active and sham treatment (before therapy cycle 1/after therapy cycle 1 and before therapy cycle 2/after therapy cycle 2).

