## **Study design**

The Mainz immunoadsorption study in adults with post-COVID is a single-center, randomized, controlled, single-blind study with a cross-over design that aims to investigate the potential effect of immunoadsorption therapy on symptom burden in people with post-COVID. The study is being conducted by an interdisciplinary team of investigators.

Included subjects are first randomized to receive either 5 verum treatments (immunoadsorption with TR-350 adsorber) or 5 sham treatments (connection to the Plasauto Sigma without adsorber). All subjects will receive both the real treatment and the sham treatment unless they decide against the respective therapy cycle before the start of the respective therapy cycle. Randomization is only used to determine which treatment is given first.

Participating subjects may withdraw from the study at any time, including after the first therapy cycle or before the second therapy cycle.

The subjects are blinded because they do not know whether the treatment is being carried out with or without an adsorber, and it is also not apparent to the subjects, as the TR-350 adsorber and Plasauto Sigma are set up behind a curtain that is not visible to the patient and remain there throughout the treatment.

The blinding of the subjects serves to assess the actual effect of the therapy without the influence of the therapy arm on the patients' reports. Since the therapeutic effects in the present study are predominantly measured using self-report instruments, such an approach seems essential to minimize the influence of distortions caused by psychological effects of the verum therapy on the study results.

[figure not shown]

1 Figure Study design and flow chart

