## **Biometrics**

In a published post-COVID cohort from Germany (Lier et al., Frontiers Neurol 2022, DOI: 10.3389/fneur.2022.988359), the median MoCA score was 27 with a interquartile range of 25 to 28. The null hypothesis is that immunoadsorption cannot reduce the score by 2 points, i.e., below the MoCA threshold. To achieve a power of 90%, according to a calculation using the G*Power Version 3.1.9.7 utility program (Faul et al., Behav Res Methods 2009), two treatment groups of 19 subjects each are required (effect size 1.0, one-sided Wilcoxon Mann-Whitney test with alpha level 0.05 and 1:1 randomization). To account for possible dropouts, the number of cases is set at 2x 20 subjects.

1. **Data management and data protection**

- Laboratory parameters will be collected. In addition, patients will complete questionnaires that allow conclusions to be drawn about their quality of life, symptom burden, cognitive abilities, and resilience in everyday life.
- Medical examinations will be carried out to assess lung function, strength, central and peripheral nervous system function, heart rhythm, and vital signs.
- Patient data and other information about blood samples and the findings of the above-mentioned examinations will be archived in a pseudonymized, password-protected database.
- The data and samples can therefore only be traced back using a key that is accessible only to the study director and the medical director of the First Medical Clinic. The data is labeled with the same key as the samples. The requirements of medical confidentiality and data protection are therefore ensured within the framework of this study.
- The data will not be passed on to third parties. The data will be stored for 10 years.
  - The data will be stored in pseudonymized form.
  - Consent can be revoked at any time in writing or verbally without giving reasons.

1. **Handling of biomaterials**

- Patient data and other information about the blood samples and the examination findings will be archived in pseudonymized form in a computerized database.

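### The 90% power belongs to a parallel-group test, but the trial is a crossover, and the protocol does not specify a within-patient verum-versus-sham contrast

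*Protocol*

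**What the plan says.** The Study design section calls the trial a "single-blind study with a cross-over design" and states: "All subjects will receive both the real treatment and the sham treatment". The sentence goes on to except patients who decline a cycle before it starts, and the section allows withdrawal between cycles. The random draw decides the order alone, and section 9.5 repeats this.

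Biometrics cites a published cohort in which "the median MoCA score was 27 with a interquartile range of 25 to 28" and takes a 2-point shift as the target: "The null hypothesis is that immunoadsorption cannot reduce the score by 2 points". It then concludes: "two treatment groups of 19 subjects each are required (effect size 1.0, one-sided Wilcoxon Mann-Whitney test with alpha level 0.05 and 1:1 randomization", for 90% power. To allow for dropouts, "the number of cases is set at 2x 20 subjects". It gives no correlation between repeat measurements and no SD of within-patient differences.

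Section 6.1 lists six scores and words the primary analysis as "comparison before and after active treatment and before and after sham treatment". The summary at the front of the protocol says the same in nearly the same words.

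**The concern.** In this design the randomized groups are two sequences, not two treatments. Each patient who completes both cycles supplies a verum result and a sham result. A Mann-Whitney test of two treatment groups of 19 takes the results as coming from different people. That fits a parallel-group trial, or a crossover analysed on the first period alone, so the stated power does not belong to the design described.

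The endpoint wording does not close the gap. Comparing before with after under verum, and before with after under sham, gives two answers but no stated contrast between them. If the two were analysed separately, a verum improvement could not be told apart from placebo response, test practice, natural recovery or period effects. The Study design section justifies the sham and the blinding by the need to remove psychological influences on self-report. Only a direct verum-versus-sham comparison does that.

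**Working it through.** **1. Inputs**
- From Biometrics: effect size 1.0, 19 per group, one-sided alpha 0.05, a 2-point target, IQR 25 to 28.
- Derived: SD = (28 − 25)/1.349 = 2.22 if scores are normal, which gives d = 2/2.22 = 0.90. The stated d = 1.0 for 2 points corresponds to SD 2.0.
- Assumed: correlation r between repeat measurements of one patient, equal for all pairs, from 0 to 0.8. The protocol gives no value.

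**2. Reproducing the stated figure**
The method is noncentral t power for two independent groups, with n multiplied by 3/π for the Wilcoxon-Mann-Whitney test under a normal parent.
- Effective n per group = 19 × 3/π = 18.14; df = 2 × 18.14 − 2 = 34.3.
- Noncentrality = 1.0 × √(18.14/2) = 3.01; one-sided critical t = 1.69.
- Power = 90.4%, and 19 is the smallest n that reaches 90%.

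The arithmetic is right for two independent groups. With d = 0.90 from the quoted IQR, the same test has 84% power one-sided and 75% two-sided.

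**3. Power of a contrast that fits the design**
For each patient take D = (change in period 1) − (change in period 2), and compare D between the two sequence groups.
- If verum beats sham by τ, the mean of D is +τ plus a period term in one sequence and −τ plus the same period term in the other. The period term cancels between the groups, and the difference in means is 2τ = 4 points.
- Each change has variance 2σ²(1 − r). With equal correlations the two changes are uncorrelated, so SD(D) = σ√(4(1 − r)).
- Effect size = 4/SD(D), with σ = 2.22 and 19 per sequence, and the same power method as in step 2.

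| r (assumed) | SD(D) | Effect size | Power, one-sided 0.05 | Power, two-sided 0.05 |
|---|---|---|---|---|
| 0 | 4.45 | 0.90 | 84% | 75% |
| 0.2 | 3.98 | 1.01 | 91% | 84% |
| 0.3 | 3.72 | 1.08 | 94% | 88% |
| 0.5 | 3.15 | 1.27 | 98% | 96% |
| 0.8 | 1.99 | 2.01 | >99% | >99% |

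At r = 0 this contrast does no better than the unpaired test at the same SD. The gain depends on a correlation that the protocol does not state.

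**4. Pooling all verum and all sham scores in the unpaired test**
A simulation (4,000 runs, 38 pairs of single scores, nominal one-sided 5%) gave a type I error of 1.2% at r = 0.5. Power at d = 0.5 was 74%, against 90% for the paired Wilcoxon test. That use of the test is conservative and wastes the pairing.

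**The case against.** **A Mann-Whitney test can be valid in a crossover.** It is valid on period differences between sequence groups, or on period 1 alone. That is correct, but Biometrics states neither. It speaks of treatment groups, and the only variability it cites is the spread of scores in a cohort. That d = 1.0 was derived from that spread is an inference, since the IQR gives about 0.90.

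**A statistical analysis plan may define the contrast.** This stands in part. A reader might infer that verum is never tested against sham, but the documents support only that this protocol does not specify such a test. A later plan would still leave the protocol's design, endpoint wording and power statement at odds.

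**The endpoint wording is ambiguous.** It can be read as setting the verum change against the sham change. A reader might go further and attach a high false-positive rate to separate before/after tests. The documents do not support a figure: they name no before/after test and give no size for a shared gain. A MoCA practice gain would also raise the score, whereas the written hypothesis concerns a reduction.

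**The sample size is not shown to be short.** This stands. A reader might infer an underpowered trial from the mismatch, but step 3 does not show one.

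**Not every patient will supply both courses.** This also stands. Patients may decline a cycle, so 38 complete pairs are not assured.

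**Conclusion.** The point holds as an internal mismatch. The design is a crossover with random order; the stated test and power are those of two independent groups; and the primary comparison names no within-patient verum-versus-sham contrast. No section reconciles the three.

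The 90% is correct arithmetic (90.4%) for a parallel-group or first-period-only comparison at d = 1.0. For the change-minus-change contrast, one-sided power with 38 completers runs from 84% to over 99% as r goes from 0 to 0.8, and passes 90% at about r = 0.2. These values assume normal scores with SD 2.22, equal correlations, 19 complete pairs per sequence and no carryover.

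The harm lies in the inference. As worded, a change under verum could be reported as the primary result without a comparison with sham. The choice of a one-sided or two-sided test and the handling of carryover are separate matters.

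**What to change.** In the summary, section 6.1 and Biometrics:

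1. Define the primary comparison as each patient's change under verum minus the same patient's change under sham.
2. Name a crossover analysis that accounts for period. Examples are a Mann-Whitney test on within-patient period differences between the two sequence groups, or a period-adjusted mixed model.
3. Restate the power for that test with 40 patients. Give the assumed within-patient correlation or SD of differences, show a range, and allow for patients who skip a cycle.
4. Make before/after results within each treatment descriptive.

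The cost is text in three places. No extra patients, visits or measurements are needed: the examination table already schedules testing after cycle 1 and before and after cycle 2, with the evaluation examination serving for most tests as the value before cycle 1. The one drawback is a power figure that rests openly on an assumed correlation.

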| Anthropometry | Yes | E |
| Vital signs (HR, RR, temp., respiratory rate) | no | E, T1, T2 |
| 12-channel ECG | Yes | E |
| Spirometry | Yes | E, nT1, vT2, nT2, F |
| Neurological examination | Yes | E, nT1, vT2, nT2, F |
| Neurocognitive testing | Yes | E, nT1, vT2, nT2, F |
| PCFS score | No | E, nT1, vT2, nT2, F |
| Chalder fatigue scale | no | E, nT1, vT2, nT2, F |
| Bell score | No | E, nT1, vT2, nT2, F |
| MRC score | no | E, nT1, vT2, nT2, F |
| Blood sampling | yes | E, T1, nT1, T2, vT2, nT2, F |
| Urine analysis | Yes | E, nT1, vT2, nT2, F |
| Cranial MRI | yes | E |
| Psychological questionnaires | yes | E, nT1, vT2, nT2, F |

Table2 : Overview of examinations performed, proportion of examinations whose results can be used from the Gutenberg Long COVID study as part of the evaluation examinations, and when the respective examinations are performed. (E = evaluation examinations; T1 = during therapy cycle 1; T2 = during therapy cycle 2; vT1 = before therapy cycle 1; nT1 = after therapy cycle 1; vT2 = before therapy cycle 2; nT2 = after therapy cycle 2, F = follow-up; for most examinations, the evaluation examination is equivalent to the examination before therapy cycle 1).

- 1. Informing participants about examination results

After each examination, the test subjects will receive brief information if there are any relevant examination results. After completion of the study, participants will receive a detailed written report of the findings and an appointment will be offered to discuss the findings.

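### The only test the protocol names is an unadjusted two-group rank test, so the scheduled pre-cycle score is not used as a covariate and some precision is given up

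*Protocol*

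**What the plan says.** Biometrics gives the calculation as "effect size 1.0, one-sided Wilcoxon Mann-Whitney test with alpha level 0.05 and 1:1 randomization", from which "two treatment groups of 19 subjects each are required" for 90% power on MoCA, raised to 20 per group for dropouts. No covariate or analysis model is named there, and the only other statistical detail in the protocol is the software. The paragraph does not say whether the test is applied to post-cycle scores, to changes or to within-patient differences.

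Section 6.1 lists six primary scales "and comparison before and after active treatment and before and after sham treatment". The Study design section describes a cross-over in which randomization sets only the order of verum and sham.

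Table 2, under Medical-technical examinations, schedules MoCA as "Neurocognitive testing | Yes | E, nT1, vT2, nT2, F" and gives PCFS, Chalder and Bell the same time points. Its legend lets the evaluation visit (E) stand in for the value before cycle 1 (vT1) for most examinations. Two primary scales are less clear. MFI-20 has no row in Table 2, although Tables 3 and 4 list it. Strength measurement is uncertain after item 2 of the amendments, which limits the neurological examinations to pain and MoCA.

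**The concern.** The endpoints are defined through the pre-cycle score, and for four of the six scales that score is on the schedule. The one named test leaves two routine ways of handling it: ignore it and compare post scores, or subtract it and compare changes. Each is efficient only at one extreme of the pre/post correlation, which the protocol does not give. Post scores waste information when the correlation is high. Changes add noise when it is below 0.5. Covariate adjustment avoids having to guess.

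Chance imbalance matters too at this size. With 19 per group, the standard error of the baseline mean difference is √(2/19) = 0.32 SD. At a correlation of 0.5, an imbalance of that size shifts a post-score comparison by 0.5 × 0.32 = 0.16 SD and a change-score comparison by the same amount in the opposite direction.

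**Working it through.** **Inputs from Biometrics.** Effect size d = 1.0, one-sided alpha 0.05, 19 per group, Wilcoxon-Mann-Whitney test. **Assumed.** Pre/post correlation ρ, shown at 0.3, 0.5 and 0.7 because the protocol gives none; normal scores with equal SD.

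**Step 1: reproduce the plan.** Use noncentral-t power with n multiplied by the Wilcoxon efficiency 3/π. The effective n is 19 × 0.955 = 18.1, and the noncentrality is 1.0 × √(18.1/2) = 3.01. Power is 0.904, and 19 is the smallest group size that reaches 90%. The plan's figure reproduces.

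**Step 2: two-group layout.** Relative to the post score, the variance factor is 2(1 − ρ) for a raw change and 1 − ρ² for a baseline-adjusted score. The effect size is divided by the square root of that factor.

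| ρ | factor, change | factor, adjusted | power, post | power, change | power, adjusted | n per group, adjusted |
|---|---|---|---|---|---|---|
| 0.3 | 1.40 | 0.91 | 0.904 | 0.802 | 0.926 | 18 |
| 0.5 | 1.00 | 0.75 | 0.904 | 0.904 | 0.961 | 15 |
| 0.7 | 0.60 | 0.51 | 0.904 | 0.985 | 0.994 | 10 |

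The last column is the group size for 90% power. A simulation with 19 per group agrees: post / change / adjusted 0.90 / 0.80 / 0.93, 0.90 / 0.89 / 0.96 and 0.89 / 0.98 / 0.99. Adjustment is never worse in variance, because 1 − ρ² ≤ 1 and 1 − ρ² = (1 − ρ)(1 + ρ) ≤ 2(1 − ρ).

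**Step 3: within-patient layout, all scores equally correlated.** Let D be the difference between the two post scores and B the difference between the two pre-cycle scores.
- Var(D) = Var(B) = 2σ²(1 − ρ).
- Cov(D, B) = σ²(ρ − ρ − ρ + ρ) = 0.
- Raw changes therefore have variance 4σ²(1 − ρ), twice that of post scores. The interval is √2 = 1.41 times as wide.
- Adjustment leaves the variance at 2σ²(1 − ρ).

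With SD 2, ρ = 0.5 and 38 patients, the standard error is √(4/38) = 0.324 for post scores and √(8/38) = 0.459 for changes. A simulation with period in the model gives 0.324 (post), 0.328 (adjusted) and 0.465 (change).

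**Step 4: within-patient layout, same-cycle correlation higher.** Take 0.7 within a cycle and 0.5 between cycles, in units of σ².
- Post: Var(D) = 2(1 − 0.5) = 1.00, and Var(B) is the same.
- Cov(D, B) = 2(0.7 − 0.5) = 0.40.
- Adjusted: 1.00 − 0.40²/1.00 = 0.84.
- Change: 1.00 + 1.00 − 2 × 0.40 = 1.20.

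Here adjustment beats both alternatives. Its interval is √0.84 = 0.92 times that of post scores.

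**The case against.** The strongest objection is that the test appears only as an input to the sample-size calculation. Nothing says the endpoints will be analysed without baseline, and covariates are commonly left to a statistical analysis plan, which may exist. This stands as a limit: a reader might infer that the protocol commits to an unadjusted analysis, and the text does not go that far. The point survives because this is the only test the protocol states, and it can be improved with values already scheduled.

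A reader might also infer that the pre-cycle score cannot be used at all. That is too strong. The test can be run on changes, which is what the wording of section 6.1 suggests, or on baseline-adjusted residuals or period differences. Nor does the point cover every primary scale, given the gaps for MFI-20 and strength.

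The second objection concerns the design. The trial is a cross-over, and with equal correlations the covariate gains nothing over post scores (0.328 against 0.324 above). This also stands. The rise from 90% to 96% belongs to the two-group layout and should not be carried over. Simulated within-patient power at d = 1.0 is at least 0.999 for correlations of 0.3 to 0.7, so pairing the periods gains far more than adjustment does. Whether to pair is a separate question.

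Finally, one might argue that the narrow MoCA interquartile range of 25 to 28 makes a correlation below 0.5 likely. A spread at one time point does not determine a pre/post correlation, so no value is favoured here.

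**Conclusion.** The point holds as a modest matter of efficiency, not as an error in the sample size. The unadjusted test meets its stated 90% under the plan's own inputs, and the documents do not support reading this point as a shortfall in power.

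In the two-group layout, adjustment adds about 2 points of power at a correlation of 0.3, 6 at 0.5 and 9 at 0.7 over post scores. It also protects against the fall to about 80% that raw changes would bring at 0.3. In a within-patient analysis the main benefit is avoiding raw changes. There is a gain over post scores only when same-cycle scores correlate more strongly than cross-cycle scores.

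Apart from about one degree of freedom, adjustment is never less precise than either alternative in either layout. The figures rest on assumed correlations, normal scores of equal variance and no carry-over.

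**What to change.** State in Biometrics that the verum-sham difference on each primary scale is estimated from post-cycle scores with the pre-cycle score as covariate:

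- **First-period, two-group comparison:** a linear model for nT1 with treatment and E/vT1.
- **Both cycles:** the within-patient difference in post scores (nT1 minus nT2), with period/sequence and the difference in pre-cycle scores (E/vT1 minus vT2) as covariate.
- **Sensitivity analyses:** a rank-based version, because the scales are bounded, and an analysis that does not use vT2. That value is measured after the first treatment, so carry-over could affect it.

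Raw before/after changes can stay as descriptive summaries. The schedule should also make clear whether MFI-20 and strength have a pre-cycle value.

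The cost is a few sentences and slightly more analysis, with no new visits, data or patients. The downsides are one degree of freedom, a linearity assumption on bounded scores and the carry-over caveat for vT2.

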**15. Publication rules**

The results will be published at national and international conferences and in specialist journals with an editorial board and review process.

**Ammendments to the Mainz immune adsorption study in adults with post-COVID (IAMPOCO)**

1. Study participants do not necessarily have to have participated in the Gutenberg Post-COVID Study prior to participating in the study, but may also be included if comparable examinations and assessments have been carried out by post-COVID outpatient clinics or post-COVID specialist practices.

2. The only neurological examinations carried out as part of the study are pain assessment using a numerical analog scale and cognitive assessment using the MocA.

3. Anticoagulation for both immune adsorption and sham treatment is achieved using citrate anticoagulation and continuous heparin administration at 1000iE/h.

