To objectively assess neurological symptoms, neurological examinations will be performed on each study participant. The initial examination will take place when participants enroll in the Gutenberg Long COVID study. To determine the possible effects of the therapy on neurological symptoms, identical examinations will also be performed after each therapy cycle.

*Vibration sensitivity*

The vibration perception threshold is measured using a tuning fork on the metatarsophalangeal joint of the big toe as an indication of a possible sensory disorder.

*Force measurement*

Muscle strength is determined, for example, by measuring the pressure exerted by the hand muscles when squeezing a rubber balloon with the dominant hand. The force applied is measured using a vigorimeter.

*Smell test*

The smell test is performed using a test battery of standardized smell sticks containing eight different smells.

*Testing pain sensitivity*

Pain sensitivity is tested using a pinprick stimulator and the sensation of pressure pain is measured using a Wagner pressure pain algometer.

- - - 1. Neurocognitive testing

Various neurocognitive functions are tested using the Montreal Cognitive Assessment (MoCA). This is a ten-minute test with various tasks that can be scored with a total of up to 30 points. It tests abilities in the areas of memory, attention, verbal abstraction, visuospatial abilities, concentration, and language comprehension.

- - - 1. Post-COVID-19 Functional Status Scale (PCFS)

The PCFS is a self-assessment tool that helps to objectively measure and compare the severity of symptoms experienced by people with post-COVID. Patients are asked to describe their condition or fill out a questionnaire. Each condition is assigned a value. The greater the severity of the symptoms described by the condition, the higher the point value on a scale of 0-4. The PCFS has been validated on cohorts of post-COVID patients and is therefore particularly suitable for assessing symptom severity.

- - - 1. Assessment of the severity of fatigue symptoms

Three different questionnaires are used to objectively assess fatigue symptoms and the resulting limitations in everyday life. These are the Chalder Fatigue Scale, the Bell Score, and the Multidimensional Fatigue Inventory (MFI-20).

- - - - 1. *Chalder Fatigue Scale*

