9.4 Timeline for individual study participants

[figure not shown]

2 : Flowchart of the schedule for individual study participants

| Examination | Duration |
| --- | --- |
| Neurocognitive testing | 15 |
| PCFS score, Chalder Fatigue Scale, Bell Score, MFI-20 | 10 minutes |
| MRC score | 5 |
| Blood sample | 5 |
| Measurement of vital signs | 10 |

Table3 : Duration of examinations in the evaluation examination block

| Examination | Duration |
| --- | --- |
| Inpatient stay | 7 days, including the following measures |
| Neurocognitive testing | 15 minutes |
| PCFS score, Chalder Fatigue Scale, Bell Score, MFI-20 | 10 |
| MRC score | 5 |
| Blood sample | 5 |
| Measurement of vital signs | 10 |
| Neurological examination | 15 |
| Spirometry | 10 |
| If venous cannulation is not possible: Shaldon device | 15 |
| Venous cannulation | 5 |
| Extracorporeal therapy 1 | 240 |
| Venous cannulation | 5 |
| Extracorporeal therapy 2 | 240 |
| Venous cannulation | 5 |
| Extracorporeal therapy 3 | 240 |
| Rest day |  |
| Extracorporeal therapy 4 | 240 |
| Day off |  |
| Extracorporeal therapy | 240 |

Table4 : Duration of examinations and interventions in the block "7-day inpatient stay for therapy cycle 1" and "9-day inpatient stay for therapy cycle 2"; blood samples indicated above as being taken before or after therapy are taken during extracorporeal therapy to avoid additional punctures.

| Examination | Duration |
| --- | --- |
| Medical history interview | 30 |
| Neurocognitive testing | 15 |
| PCFS score | 10 minutes |
| MRC score | 5 |
| Blood sampling | 5 |
| Measurement of vital signs | 10 |
| Neurological examination | 15 |
| Spirometry | 10 |

Table5 : Duration of examinations in the "Follow-up visit 4 weeks" block

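### Strength, one of the six primary measures, loses its only described and scheduled test under amendment item 2, yet stays in the endpoint list

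*Protocol*

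**What the plan says.** **Endpoint.** Section 6.1 and the project summary list PCFS, Chalder, MoCA, MFI-20, Bell and "Strength measurement" as primary. Section 6.1 sets the comparison at "before treatment cycle 1/after treatment cycle 1 and before treatment cycle 2/after treatment cycle 2".

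**Test.** Under Medical-technical examinations, the neurological part opens with "To objectively assess neurological symptoms, neurological examinations will be performed on each study participant". It then describes four tests: vibration, force, smell and pain sensitivity. The force item reads "Muscle strength is determined, for example, by measuring the pressure exerted by the hand muscles when squeezing a rubber balloon with the dominant hand", with a vigorimeter as the instrument.

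**Schedule.** Table 2 has no strength row. It has one row for the neurological examination, at E, nT1, vT2, nT2 and F. In section 9.4, Tables 4 and 5 also give only a 15-minute neurological examination.

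**Amendment.** Item 2 states "The only neurological examinations carried out as part of the study are pain assessment using a numerical analog scale and cognitive assessment" by MoCA.

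**Text left unchanged.** The data management list that follows the Biometrics paragraph still includes strength among the things to be examined.

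**Fatigue scales (minor).** Table 2 has separate rows for PCFS, Chalder ("Chalder fatigue scale | no | E, nT1, vT2, nT2, F") and Bell, and none for MFI-20. Tables 3 and 4 list all four scales together. Table 5, for the 4-week follow-up, shows only "PCFS score | 10 minutes".

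**The concern.** A primary measure needs a defined test and fixed times. For strength both came from the neurological examination, and the amendment cuts that examination down to two items that do not include it. The endpoint list was not amended with it.

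Site staff who follow the amendment would stop taking grip readings, while the analyst working from section 6.1 would expect four readings per subject. A reading missed after a cycle cannot be taken later. If some subjects are tested and others are not, the strength comparison would rest on an unplanned subset, and a reader of the results could not tell whether the endpoint was dropped by design or went missing.

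**Working it through.** This is a check of the sections against each other. Arithmetic enters only in the count and in confirming that the sample size is not involved.

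**1. Is the amendment operative text?** Yes. It gives rules in the present tense. Item 1 changes who may enter, item 2 the examinations, item 3 the anticoagulation. It does not summarise superseded wording.

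**2. Each primary measure against its test and schedule, after the amendment:**

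| Measure (6.1) | Named or described as in use | Scheduled | After item 2 |
| --- | --- | --- | --- |
| PCFS | yes | Table 2; Tables 3 to 5 | unchanged |
| Chalder | yes | Table 2; Tables 3 and 4 | unchanged |
| MoCA | yes | Table 2 (neurocognitive testing); Tables 3 to 5 | expressly kept |
| MFI-20 | yes, as one of three fatigue questionnaires | Tables 3 and 4; no Table 2 row | unchanged |
| Bell | yes | Table 2; Tables 3 and 4 | unchanged |
| Strength | yes, only among the neurological tests | only through the neurological examination | not on the retained list |

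Count: 6 listed − 1 = 5 still planned, so 1 of 6 has no assessment.

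**3. How widely does item 2 use the word neurological?** The body of the protocol puts the MoCA under its own heading, neurocognitive testing, with its own Table 2 row. Item 2 nevertheless counts the MoCA as a neurological examination. It therefore uses the term broadly, which makes it harder to argue that a test the body places directly among the neurological examinations falls outside it.

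**4. Is the sample size affected?** The Biometrics section uses the MoCA: effect size 1.0, one-sided Wilcoxon-Mann-Whitney test, alpha 0.05, power 90%, giving 19 per group. To reproduce this, apply the asymptotic relative efficiency 3/π to the t-test:

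- effective n per group = 19 × 3/π = 18.14
- noncentrality = 1.0 × √(18.14/2) = 3.01
- degrees of freedom = 2 × 18.14 − 2 = 34.3
- power = 0.904

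Nineteen is the smallest n per group that reaches 0.90 by this method. The figure reproduces, and strength plays no part in it.

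**The case against.** **Strength may survive as a general medical test.** The data management list names strength as an item apart from nervous-system function, so the grip test could be read as outside item 2. That reading is possible. But the list neither describes a test nor gives a time for one, and no other section does so outside the neurological examination. If retention was intended, the document has to say so. Reconciliation is needed on either reading.

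**A reader might infer that MFI-20 is also uncollected, making two of six.** The documents do not support this. Section 6.1 fixes its before and after timing, the examination section names it among the three fatigue questionnaires in use, and Tables 3 and 4 list it at evaluation and in both therapy stays. What remains is a missing row in Table 2, and a Table 4 entry that does not say whether the scale is completed before the cycle, after it, or both.

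**A reader might infer that follow-up fatigue data will be missing for every scale.** This is not supported either. The descriptions of Chalder and Bell and their Table 2 rows both require them at follow-up. Table 5 is a table of durations, and its PCFS entry carries the same 10 minutes that the four-scale bundle has in Tables 3 and 4, so it may be a shortened label, though that cannot be proved. Follow-up is also not one of the primary comparisons in section 6.1.

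**The power calculation is untouched.** This is true and it limits the consequence. It does not supply the missing test.

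**Conclusion.** The point holds for strength: one of six primary measures has no described or scheduled assessment once amendment item 2 applies. Followed literally, this affects all 40 planned subjects. The conclusion rests on two readings: that the amendment is in force, and that it covers the grip test because the protocol describes that test only among the neurological examinations. If the investigators meant to keep the test, the fault is one of wording alone, but the wording still has to change because staff cannot infer the exception.

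The missing MFI-20 row in Table 2 and the short Table 5 are minor inconsistencies and do not amount to lost primary endpoints. The sample size stands.

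**What to change.** Choose one of the following for strength, before further cycles are completed without a reading:

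- **Drop it.** Delete strength from the project summary and section 6.1, and align the data management list. Cost: one primary measure fewer. If readings already exist, say how they will be reported.
- **Keep it.** State in amendment item 2 that the hand-grip vigorimeter test is retained, and give it its own Table 2 row at E/vT1, nT1, vT2 and nT2. Cost: a short test at each of these times. Because item 1 now admits subjects from outside the Gutenberg study, whose earlier work-up may not include this test, the starting value should be measured within the trial where it is not already available.

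In the same amendment, add an MFI-20 row to Table 2 matching Chalder and Bell (E, nT1, vT2, nT2, F). Align Table 5 with Table 2 and with the descriptions of Chalder and Bell, which already require both at follow-up. These are wording changes; Tables 3 and 4 already allow 10 minutes for the four questionnaires together.
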